# Efficacy and Mechanism of Acupoint Catgut Embedding in the Treatment of Chronic Spontaneous Urticaria: Protocol for a Randomized Double-Blind Placebo-Controlled Trial

**DOI:** 10.2196/54376

**Published:** 2024-07-31

**Keywords:** chronic spontaneous urticaria, acupoint catgut embedding, functional magnetic resonance imaging, randomized controlled trial, mechanism of action

## Abstract

**Background:**

Chronic spontaneous urticaria (CSU) is a common chronic inflammatory skin disease that manifests as itching and wheals, seriously affecting quality of life. Clinical observations and previous research trials have shown that acupuncture is safe and effective for the treatment of CSU. However, there are problems, such as a short duration of action and frequent treatment. Compared with traditional acupuncture, acupoint catgut embedding (ACE) has the advantages of a longer effect and higher compliance. Clinical trials are needed to prove its efficacy and mechanism of action.

**Objective:**

This trial aims to provide definitive evidence for the treatment of CSU with ACE and explore the mechanism of ACE.

**Methods:**

This is a randomized, double-blind, placebo-controlled trial. In this trial, 108 participants aged 18-60 years with a diagnosis of CSU and no history of ACE will be randomly assigned to 2 groups (1:1 ratio) using the Statistical Analysis System: treatment (ACE) and control (sham ACE). The participants and efficacy evaluators will be blinded to the grouping. Both the ACE and sham ACE groups will undergo acupuncture, but the sham ACE group will not receive catgut sutures. Treatment will be performed twice weekly for 8 weeks, with a 1-week run-in period and a 16-week follow-up period. Twenty patients will be randomly selected to undergo functional magnetic resonance imaging before and after the treatment period. The primary outcome will be the urticaria activity score over 7 days (UAS7). We will use R (version 4.0.1; R Project for Statistical Computing) to perform ANOVA and independent samples *t* tests to compare the differences within and between groups before and after treatment by judging the rejection range based on a significance level of .05.

**Results:**

The study protocol has been approved by the Ethics Committee of Guang’anmen Hospital on September 7, 2022, and has been registered on November 30, 2022. Recruitment began on March 1, 2023. A total of 4-6 participants are expected to be recruited each month. The recruitment is planned to be completed on March 1, 2025, and we expect to publish our results by the winter of 2025. As of November 1, 2023, we have enrolled 25 participants with CSU.

**Conclusions:**

This randomized, double-blind, placebo-controlled trial aims to provide definitive evidence for the treatment of CSU with ACE and explore the mechanism of ACE. We hypothesize that wheals and itching will show greater improvement in participants receiving active therapy than in those receiving sham treatment. The limitations of this study include its single-center trial design, small sample size, and short treatment duration, which may have certain impacts on the research results.

**Trial Registration:**

Chinese Clinical Trial Registry ChiCTR2200066274; https://www.chictr.org.cn/showprojEN.html?proj=179056

**International Registered Report Identifier (IRRID):**

DERR1-10.2196/54376

## Introduction

Chronic spontaneous urticaria (CSU) is a common chronic inflammatory skin disease that accounts for 90% of all chronic urticaria cases. It manifests as itching and wheals with continuous or intermittent attacks for more than 6 weeks. Angioedema accompanies 40% of cases of CSU, with 10% primarily presenting with angioedema [1,2]. CSU has no clear inducing factors, and a single episode usually disappears within 24 hours. The majority of individuals with this condition experience a disease duration of 2 to 5 years, often with self-limiting tendencies. However, in 20% of cases, the disease persists for more than 5 years, and 1.4% endure it throughout their life [3,4].

The pathogenesis of CSU is complex, and currently, it is mainly thought to be related to 2 types of autoimmune reactions: type I autoimmune reaction, which is caused by immunoglobulin E, and type IIb autoimmune reaction, which is caused by immunoglobulin G autoantibodies [5]. Recent studies have shown that factors, such as skin mast cell degranulation [6,7], basophil activation [8], and other serological factors, can also induce vasodilation, increase vascular permeability, stimulate sensory nerve endings, and lead to skin swelling, redness, and pruritus. However, the specific pathogenesis of CSU remains unclear. When considering patients who develop the disease without the influence of external triggers, it becomes evident that the primary factor at play is the disruption of internal regulatory mechanisms within the human body. Clinical observations have found that the psychological factors of patients, such as anxiety and depression, have an impact on the onset of urticaria [9]. CSU is characterized by repeated attacks that are prolonged and difficult to cure, which seriously affect the quality of life of patients [10], bring mental and psychological pressure to patients, and further aggravate the occurrence of CSU [11], forming a vicious circle.

Currently, there are no effective radical treatments for CSU. First-line treatment revolves around standard doses of second-generation H1 antihistamines. Second-line treatment involves combinations of medications, often in high doses. Third-line treatment primarily consists of cyclosporine and biologic agents [3], which have problems such as long drug cycles, easy recurrence of drug withdrawal, and obvious side effects. Traditional Chinese medicine (TCM) is widely used as a complementary and alternative therapy to treat CSU [12].

Research has confirmed that the skin is both an immediate stress perceiver and a target of stress responses [13]. The psychological stress resulting from depression, anxiety, and other illnesses can ultimately lead to the development of CSU by exerting its effects on the skin through intricate neural systems. These systems include the activation of neuropeptides and neurokinins, the mediation of inflammatory mediators and cells, and the regulation of hypothalamic-pituitary-adrenal (HPA) axis hormones [14]. Neural metabolites or neurotransmitters released by the brain cause changes in skin function through the HPA axis. Abnormalities in the HPA axis can stimulate mast cells, which are the main effector cells of CSU, to release histamine. In addition, brain-derived neural metabolites can mediate or enhance skin inflammation.

In the TCM theory, all painful and itching sores are ascribed to the heart, which stores the spirit. This is consistent with the modern medical theory of urticaria and its associated psychological factors. The TCM theory can be integrated with modern medical research. TCM frequently uses treatments like herbal medicine and acupuncture in the clinical management of CSU. These treatments aim to nourish the heart, soothe the spirit, purge heart fire, and alleviate feelings of anxiety and depression. However, some patients may experience adverse reactions to herbal medicine, and the bitter taste of the medicine may intensify these reactions. These reactions can lead to resistance and increased psychological stress, potentially exacerbating their condition. Consequently, it is recommended to explore alternative therapies, such as acupuncture, as soon as possible.

In 2018, we selected acupoints related to the heart channel and conducted a randomized, double-blind, placebo-controlled clinical observational study titled “Treatment of CSU by acupuncture from the heart.” We enrolled 60 subjects and divided them randomly into 2 groups (a “treatment group” that received acupuncture and a “control group” that received oral loratadine only) for a 6-week study of acupuncture treatment performed 3 times weekly. As the treatment duration progressed, both groups exhibited improvements, with a significant reduction in the urticaria activity score over 7 days (UAS7). In addition, we used functional magnetic resonance imaging (fMRI) to reveal the brain mechanisms of CSU, and acupuncture was found to alleviate itch through a cerebellar reward-somatosensory circuit for the first time [15,16]. However, traditional acupuncture therapy has a short action time, a long treatment cycle, and many operations, which means that patients require frequent medical attention. This reduces patient compliance. Compared with traditional acupuncture, acupoint catgut embedding (ACE) has the advantages of a longer effect and higher compliance; however, there is a lack of high-quality clinical studies.

The main purpose of this research is to verify the efficacy and safety of ACE in the treatment of CSU based on the theoretical principle that “all pain and itchy sores belong to the heart.” Additionally, fMRI is used to reveal the central mechanism of ACE during CSU treatment.

## Methods

### Study Design

This study is designed as a 2-arm, randomized, placebo-controlled trial with both patients and evaluators blinded to group allocation. The study is divided into 3 phases: a 1-week run-in period, an 8-week intervention period, and a 16-week follow-up period. A total of 108 patients will be randomized into 2 groups (ACE and sham ACE groups), with 54 patients in each group. In each group, 20 patients will be selected to participate in fMRI before and after the treatment period. Additionally, we will recruit an age- and sex-matched control group of 20 healthy participants, who will undergo fMRI only before and after the treatment period. A flowchart of the trial is shown in Figure 1.

**Figure 1 figure1:**
[figure not shown]
Flowchart illustrating the randomized, placebo-controlled, double-blinded trial of acupoint catgut embedding for CSU. ALFF: amplitude of low-frequency fluctuation; CSU: chronic spontaneous urticaria; CU-Q2oL: Chronic Urticaria Quality of Life Questionnaire; DLQI: Dermatology Life Quality Index; FC: functional connectivity; fMRI: functional magnetic resonance imaging; ICA: independent component analysis; ISI: Insomnia Severity Index; SAS: Self-Rating Anxiety Scale; SDS: Self-Rating Depression Scale; UAS7: urticaria activity score over 7 days; UCT: urticaria control test.

### Eligibility Criteria

#### Inclusion Criteria

The inclusion criteria are as follows: (1) age between 18 and 60 years, regardless of sex; (2) meeting the diagnostic criteria for CSU; (3) wheals and itching occurring continuously for at least 6 weeks before enrollment (despite using H1 antihistamines; occurring at least once daily) and wheals and itching being the main symptoms (without severe systemic symptoms); (4) a UAS7 of ≥16 and a weekly pruritus score of ≥8; (5) no history of ACE; and (6) signing of informed consent and volunteering to participate in the study.

#### Exclusion Criteria

The exclusion criteria are as follows: (1) clear identification of the cause of chronic urticaria (eg, physical urticaria); (2) use of glucocorticoids, hydroxychloroquine, methotrexate, cyclosporine, cyclophosphamide, or intravenous immunoglobulins for any indication (daily or more than 3 consecutive days) within the first 30 days of enrollment; (3) use of H2 antihistamines, leukotriene receptor antagonists, omalizumab, or other biological agents in the 7 days preceding screening or 14 days before randomization; (4) exceeding the recommended dosage of H1 antihistamines within 3 days before screening; (5) presence of serious cardiovascular and cerebrovascular diseases, diabetes, abnormal bone metabolism, liver and kidney diseases, hematopoietic system diseases, systemic lupus erythematosus, other serious autoimmune diseases, other diseases, and other serious primary diseases; (6) diseases other than chronic urticaria with symptoms of urticaria or angioedema, such as urticaria vasculitis, erythema multiform, cutaneous mastocytosis (pigmentary urticaria), and hereditary or acquired angioedema (eg, due to deficiency of C1 inhibitors); (7) skin diseases related to chronic pruritus (eg, atopic dermatitis, bullous pemphigus, herpetic dermatitis, and pruritus in old age), which may affect the evaluation and treatment in the study; (8) allergy to the buried wire material; (9) fertility needs, pregnancy, or lactation during the study period; (10) contraindicating magnetic resonance imaging (MRI) findings; (11) participation in other clinical trials within the last 3 months; and (12) use of psychotropic drugs within the previous month.

#### Inclusion Criteria for Healthy People

The inclusion criteria are as follows: (1) good health; (2) no serious physical illness and no family history of mental illness; (3) no history of alcohol or drug addiction; and (4) no contraindications for MRI scanning and no structural abnormalities in the brain.

#### Withdrawal Criteria and Management

Participants may be permitted or required to withdraw from the study for the following reasons: (1) experiencing serious adverse events or adverse events during the study period; (2) demonstrating poor compliance and showing a lack of cooperation with treatment and efficacy follow-up; (3) unauthorized use of nonclinical emergency drugs without information; (4) voluntarily requesting to withdraw from the trial; and (5) withdrawal from the trial before the end of the treatment course, loss to follow-up, or death for various reasons.

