### Sample Size

Referring to relevant literature [17], a formula for the superiority test is used to calculate the sample size:

where *c*=1, *n*_2_=*n*_1_; if α=.05, *u*_1_-*T*=1.64 and *u*_1_-*u*=1.28.

According to previous research [15] based on the UAS7 as the main therapeutic evaluation index, *e* is set at 9.12, *W* is set at 6, and the data are substituted into the formula to calculate *n*_1_=*n*_2_≈40. Considering a 25% dropout rate, we establish a sample size of 54 cases in each group, with a total of 108 cases.

However, it is worth noting that when conducting MRI research on the human body, the calculation of sample size does not strictly adhere to the methods used in clinical trials. Currently, there are no clear guidelines for determining sample size in fMRI studies. After an extensive review of the literature spanning the past decade, we did not find a standardized sample size calculation method for experimental studies involving brain fMRI. The previous results of the research group showed that 20 cases in each group met the statistical and practical requirements [13,14]. In this study, 40 subjects are selected for fMRI examination based on the results of previous studies and the scale of the subjects.

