#### Concomitant Therapy

During the trial, only 1 H1 antihistamine can be taken. Other medicines or TCM with similar clinical efficacy, such as biological agents, H2 antihistamines, and hormones, must not be taken. If other therapies are combined, they will be recorded in the “Case Report Form (CRF).” If subjects require other treatments or concomitant care, they will need to contact the doctor in advance.

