### Outcomes

The study schedule is presented in Figure 3. All outcome measures explained below will be recorded from baseline until the end of follow-up.

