#### Quality Control

Prior to the trial’s commencement, all involved team members will undergo investigator training to acquaint themselves with the administration processes, clarify the procedures for embedding, and become familiar with fMRI [26]. Throughout the trial, each participant will be treated by the same surgeon. The head movement test involving blood oxygenation level–dependent (BOLD) images will be promptly conducted during the scanning process to ensure that head movement remains ≤1.2. If head movement exceeds 1.2, a new BOLD scan will be carried out. Following the scanning, data backup will be performed using both a removable hard disk and CD burning. There will be no changes in assignments, and the migration of individuals between groups will not be allowed. If participants discontinue treatment, the reasons for leaving the study will be recorded.

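### The withdrawal rule lets participants be taken out of the study, not only off treatment, after events that may relate to arm or outcome, so UAS7 may be missing informatively

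*Protocol article*

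**What the plan says.** Withdrawal Criteria and Management opens: "Participants may be permitted or required to withdraw from the study for the following reasons: (1) experiencing serious adverse events or adverse events". No threshold of severity or relatedness is attached. The list goes on to "demonstrating poor compliance and showing a lack of cooperation with treatment and efficacy follow-up" and then "unauthorized use of nonclinical emergency drugs without information". Its last two items are voluntary withdrawal, and early exit, loss to follow-up or death. The exit described is from the study throughout.

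Quality Control ties the two events together: "If participants discontinue treatment, the reasons for leaving the study will be recorded".

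Three other places bear on the point:

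- Outcomes: "All outcome measures explained below will be recorded from baseline until the end of follow-up". It does not say whether this still applies after treatment stops or after withdrawal.
- Concomitant Therapy: one H1 antihistamine is allowed and other drugs of similar effect are not. It adds "If other therapies are combined, they will be recorded in the" case report form, so extra treatment does not lead to exit in every case.
- Sample Size: "Considering a 25% dropout rate, we establish a sample size of 54 cases in each group".

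Statistical Methods names t tests and repeated-measures ANOVA. The article gives no analysis set and no missing-data method. Those may stand in a document not shown, and their absence is not part of this point.

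**The concern.** Stopping treatment and leaving the study are different events. The first need not end outcome collection, and the article's wording merges them.

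The listed reasons arise after randomisation and may not be neutral:

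- **Link to arm.** Safety Assessment gives subcutaneous nodules and haematoma among its examples of adverse events. Both arms are needled at the same acupoints, so haematoma may be similar in the two, but only the ACE arm keeps suture material in place.
- **Link to outcome.** A participant whose urticaria is uncontrolled has the most reason to take a drug that is not allowed.
- **Who decides.** The section does not say who may require withdrawal. Under Randomization, Concealment, and Blinding, the operators know the allocation.

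If UAS7 stops at such an event, the late scores that remain come from a selected part of each arm, and the selection may differ between arms. An analysis plan written later can model the missing scores but cannot recover them.

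**Working it through.** **1. The plan's own figures.** Sample Size gives 9.12 and 6, read here as SD and difference because that reading reproduces the result, with normal quantiles 1.64 and 1.28.

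- n per group = 2 × [9.12 × (1.64 + 1.28) / 6]² = 39.4, rounded up to 40.
- With 25% dropout: 40 / 0.75 = 53.3, rounded up to 54.

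Both figures reproduce. The plan therefore allows for about 54 × 0.25 = 13.5 losses per arm.

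**2. Bias if only those remaining are compared.** Let p be the proportion withdrawn in an arm, and w the number of UAS7 points by which those withdrawn would have scored worse than those remaining. The mean of those remaining is then too low by p × w. The ACE minus sham difference shifts by

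p_sham × w_sham − p_ACE × w_ACE.

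A lower UAS7 is better, so a positive shift works against ACE. The values of p and w below are assumptions; the article gives only the overall 25%.

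- Equal rate and mechanism (25% each, same w): shift 0.
- 35% sham, 15% ACE, w = 6 in both: (0.35 − 0.15) × 6 = 1.2 points against ACE, and 1.2 / 6 = 20% of the planned difference.
- The same rates reversed: 1.2 points in favour of ACE.
- Equal rates, different mechanism (25% each, w = 6 in sham and 0 in ACE): 0.25 × 6 − 0.25 × 0 = 1.5 points against ACE. Equal rates alone are not enough.

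**3. Simulation check.** 54 per arm, SD 9.12, withdrawal propensity correlated with UAS7 at 0.3, 0.5 or 0.8 (assumed), t test on those remaining, 4,000 runs per case.

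| Withdrawn, ACE / sham | True benefit | Mean estimated benefit at 0.3 / 0.5 / 0.8 | One-sided rejection at 0.05 |
|---|---|---|---|
| 25% / 25% | 0 | about 0 in all three | about 5% in all three |
| 30% / 20% | 0 | 0.4 / 0.7 / 1.0 | 7% / 10% / 15% |
| 35% / 15% | 0 | 0.8 / 1.3 / 2.2 | 11% / 16% / 33% |
| 15% / 35% | 6 | 5.2 / 4.6 / 3.8 | 82% / 77% / 70% |

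With correlation 0, the bias was about zero at every pair of rates. Harm needs both a link between withdrawal and outcome and a difference between arms.

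**4. Precision.** For 6 points and SD 9.12, power with 40 per arm is 90.3% one-sided or 83.7% two-sided at 0.05. With all 54 followed it is 96.2% or 92.8%, provided that effect and SD stay the same once off-treatment scores are included.

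**The case against.** The strongest reply is that the text is softer than it first looks.

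- The rule says participants may be permitted or required to leave, so removal is not automatic.
- The compliance item joins poor compliance with lack of cooperation in efficacy follow-up. For someone who refuses follow-up, most outcome data are lost anyway.
- The drug item concerns undisclosed use, and Concomitant Therapy provides for recording other therapies.
- Items such as death and loss to follow-up show that the list partly catalogues ways of leaving.
- Outcomes says that measures are recorded to the end of follow-up.

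All of this stands, and it limits the point to a risk. It does not remove the point. The adverse-event item has no such qualifier. Quality Control repeats the merging of treatment stop and study exit. The sentence under Outcomes does not say that it survives withdrawal.

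A reader might infer three stronger things that the article does not support:

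- **That the primary test is a comparison of completers.** No section says that withdrawn participants are excluded.
- **That inflating 40 to 54 treats the losses as ignorable.** The inflation is routine and says nothing about how losses are analysed. The 25% is also a planning allowance and not a ceiling.
- **That no analysis could help.** UAS7 recorded before exit, with stated missing-data assumptions and sensitivity analyses, can reduce or bound the bias, although it cannot replace scores never collected.

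**Conclusion.** The point holds as a risk created by stated wording. The article permits required exit from the study after adverse events of any severity, poor compliance with lack of cooperation, or unauthorised drug use, and it describes stopping treatment as leaving. Applied as written, this can end UAS7 collection for reasons related to arm or outcome.

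Neither the size nor the direction of any bias follows from the document. The range starts at about zero, for withdrawal equal in rate and mechanism. The 1.2 points for 35% versus 15% rests on assumed rates, on an assumed 6-point deficit in those withdrawn, and on an analysis of remaining participants only. It can favour either arm. The passages should be corrected, because the remedy is inexpensive and data not collected cannot be recovered later.

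**What to change.** In Withdrawal Criteria and Management and in Quality Control, define two separate events: discontinuing study treatment, and withdrawing from the study. Leave the rules for stopping treatment as they are. State that for everyone who has not withdrawn consent, the self-completed UAS7 continues to be collected to week 8 and through the 16-week follow-up. Record non-compliance and extra drug use with their dates, and do not use them to end data collection.

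The costs are modest but real:

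- Recruitment is under way (25 enrolled by 1 November 2023), so this is an amendment. Under Amendments it needs agreement and signature by all investigators, ethics approval and a registry update.
- Adherence describes weekly contact for the treatment period only, so collection during follow-up after a treatment stop needs some added contact.
- The estimate will include off-treatment scores and may be somewhat diluted.

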#### Adherence

To promote participant retention and ensure complete follow-up, the research team will initially emphasize the importance of subject compliance at the outset. The team will be in regular contact with the participants, checking on their progress once a week, providing reminders to remain engaged in treatment, and offering support throughout the treatment period. Following the completion of the full treatment regimen, participants will receive a subsidy as a token of appreciation. Participant adherence will be assessed by counting the number of treatments received, with the criterion of 80% or more of the prescribed treatments as the threshold for good adherence. The formula for calculating treatment adherence is as follows: treatment adherence = (number of treatments received by the subject / total number of treatments to be received by the subject) × 100.

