### Ethical Considerations

The study protocol complies with the ethical standards of the Declaration of Helsinki. The Ethics Committee of Guang’anmen Hospital has approved the study protocol (approval number: 2022-114-KY; September 7, 2022), which has been registered in the Chinese Clinical Trial Registry (trial registration number: ChiCTR2200066274; registered on November 30, 2022). The investigators have the responsibility to fully and comprehensively introduce the purpose, procedures, possible risks, and subsidy of this study to the participants and get signatures on 2 informed consent forms, one kept by the participant and the other kept by the researcher, which should be retained as a clinical research document for reference. The participants will receive a subsidy of 300 CNY (US $41.27) through bank transfer after completing treatment and follow-up. All participants will be free to participate in this study and can decide to withdraw at any time. During the study process, the privacy and confidentiality of the participants will be protected. Each participant’s name will be replaced by a serial number and initials. Their personal information will not be disclosed when the paper is published, and the results will be published regardless of whether the research is positive or negative.

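### Withdrawal is written as leaving the study for any adverse event, and nothing keeps those who stop treatment in UAS7 follow-up

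*Protocol article*

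**What the plan says.** All references are to the protocol article.

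- **Withdrawal Criteria and Management** opens with this rule: "Participants may be permitted or required to withdraw from the study for the following reasons: (1) experiencing serious adverse events or adverse events". The list sets no threshold of severity or relation to treatment. It offers no intermediate status of being off treatment but still in follow-up.
- **Quality Control:** "If participants discontinue treatment, the reasons for leaving the study will be recorded". The trigger is stopping treatment; what gets recorded is the reason for leaving the study.
- **Outcomes:** "All outcome measures explained below will be recorded from baseline until the end of follow-up". This is a general schedule statement and does not mention participants who have withdrawn.
- **Adherence:** the section names complete follow-up as an aim. The measures it lists include weekly contact, "providing reminders to remain engaged in treatment, and offering support throughout the treatment period", and a payment: "Following the completion of the full treatment regimen, participants will receive a subsidy as a token of appreciation".
- **Safety Assessment:** fainting, infection, haematoma and nodules are expected. A participant with such an event is monitored until it resolves. UAS7 is not mentioned there.
- **Study Design:** "a 1-week run-in period, an 8-week intervention period, and a 16-week follow-up period".
- **Sample Size:** "Considering a 25% dropout rate, we establish a sample size of 54 cases in each group".

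**The concern.** Stopping an intervention and leaving a trial are different events. A participant who stops catgut embedding because of an infected site can still fill in a UAS7 diary. If that participant is also taken out of the study, the primary outcome goes missing because of the treatment.

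The two arms are not alike in this respect. Both are needled at the same acupoints, but only ACE leaves a suture in place (Interventions, ACE Approach), so suture reactions can occur in one arm only. Fainting, infection and haematoma can follow needling in either arm. Unequal loss is therefore possible, not certain.

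The dropout allowance protects the number analysed. It does not protect the comparability of those who remain. An analysis plan could choose how to handle missing scores, but it could not recover scores that were never collected.

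**Working it through.** **1. The plan's own figure.** Inputs from Sample Size: quantiles 1.64 and 1.28, e = 9.12, W = 6, 25% dropout. The symbols are not defined in the text, so I assume that e is the SD and W is the UAS7 difference.

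- n per arm = 2 × (1.64 + 1.28)² × (9.12/6)² = 39.4, about 40.
- 40/(1 − 0.25) = 53.3, rounded up to 54.

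Both stated figures reproduce, which supports the assumed reading. The allowance is 54 − 40 = 14 per arm. On these assumptions, one-sided power is 0.90 with 40 per arm and 0.96 with all 54. The allowance thus covers precision, and no stated figure is disputed.

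**2. Does any section keep a participant who stops treatment in UAS7 follow-up?**

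| Section | What it does | Keeps UAS7 going? |
|---|---|---|
| Withdrawal Criteria and Management | exit from the study, at discretion, for any adverse event | No |
| Quality Control | stopping treatment recorded as leaving | No |
| Outcomes | general schedule for all measures | Not stated for those withdrawn |
| Adherence | aims at complete follow-up; reminders and support concern treatment | Not stated for those withdrawn |
| Safety Assessment | follows the adverse event to resolution | UAS7 not mentioned |

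**3. Data at stake per participant.** The planned period after the run-in is 8 + 16 = 24 weeks. The text at hand names no single primary time point, so the whole schedule is counted. If leaving at week w ends collection, the share forgone is (24 − w)/24:

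| Leaves at week | Weeks forgone | Share |
|---|---|---|
| 2 | 22 | 92% |
| 4 | 20 | 83% |
| 6 | 18 | 75% |
| 8 | 16 | 67% |

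**4. Illustration of bias.** Suppose k of 54 ACE patients are lost, none are lost from sham, and those lost would have scored d points worse than those retained, whose mean is m. The full-arm mean is [(54 − k)m + k(m + d)]/54 = m + kd/54. An analysis of observed scores alone therefore makes ACE look better by kd/54.

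| k | d = 3 | d = 6 | d = 6, as a share of W = 6 |
|---|---|---|---|
| 3 | 0.17 | 0.33 | 6% |
| 6 | 0.33 | 0.67 | 11% |
| 14 | 0.78 | 1.56 | 26% |

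Both k and d are assumed. At d = 0 the shift is zero. At d = −3 or −6 the same values apply with the sign reversed, and ACE looks worse. With loss in both arms the net shift is (k₁d₁ − k₂d₂)/54, which is zero when the numbers lost and their d are equal.

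**The case against.** The best defence is that this rests on silence in a condensed article. The withdrawal wording is permissive and lists grounds; it does not mandate exit. The Quality Control sentence is a documentation instruction that may simply be loose. Elsewhere the article does tell treatment and follow-up apart: the withdrawal list names both, and Adherence counts treatments received while also aiming at complete follow-up. Safety Assessment expects ordinary reactions and follows them within the trial.

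Much of this stands, and it limits the claim. It does not remove it. Two sentences on conduct are stated, not omitted: one makes the exit a study exit, and the other records stopping treatment as leaving. Nothing else in the document overrides them for the participant concerned.

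Some stronger readings are tempting, and the documents do not support them:

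- **Every adverse event forces removal.** The text says permitted or required, so removal is a matter of discretion.
- **The result will be biased towards ACE.** There are no event rates. Nothing links the listed reactions to worse urticaria, and the article does not fix a complete-case analysis. Even the direction of any bias is unknown.
- **The subsidy drives data loss.** Payment is made "through bank transfer after completing treatment and follow-up", so someone who stops early is not promised it. Nothing shows that this costs UAS7 data, and it is a payment choice open to debate.
- **One minor reaction would stop the trial.** The first stopping criterion under Modifications sets no severity or scope. It clashes with Safety Assessment only if read at trial level; read at patient level, it does not.

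**Conclusion.** The point holds in a limited form. As written, the protocol permits or requires study exit for any adverse event and merges stopping treatment with leaving, so UAS7 data can be lost for treatment-related reasons, possibly more in one arm.

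The size cannot be derived from the document. The shares of 67% to 92% hold only if leaving ends collection. The shifts of 0.17 to 1.56 points hold only for the assumed k and positive d, with loss in ACE alone and an analysis of observed scores. The largest of them puts the whole per-arm allowance of 14 into ACE and none into sham. The case for a change is that it is cheap and closes off a possible bias, not that a bias has been shown.

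**What to change.** - **Withdrawal Criteria and Management:** state that an adverse event may end study treatment, but that the participant stays in scheduled UAS7 follow-up to the end of the 16-week period unless consent is withdrawn.
- **Quality Control:** record reasons for stopping treatment separately from reasons for leaving the study.
- **Adherence:** continue the existing contact through follow-up for those who stop treatment.

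The cost is a short amendment with ethics committee review and some extra contact. Participants already enrolled (25 by November 1, 2023, per Results) may need to be informed. UAS7 is self-recorded, so no new measurement is needed, and the sample size does not change. No change to the subsidy or to the stopping criteria is proposed.
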